##### Adherence to PA guidelines

PA type, frequency and duration measured by 8 items from the adapted version of the GLTEQ
[44,46] will be used to calculate whether or not participants are meeting the PA guidelines for cancer survivors
[10].

##### Sedentary behaviour

Sedentary behaviour is measured using a validated five item scale asking about time spent sitting (hours and minutes) each day during the week and on the weekend in the following situations (a) while travelling to and from places; (b) while at work; (c) while watching television; (d) while using a computer from home; and (e) in leisure time not including watching television (e.g. visiting friends, dining out)
[52].

##### Health related quality of life

Quality of life is measured using version 4 of the internationally validated 37-item FACT-Breast measurement system (FACT-B)
[53]. The FACT-B is multidimensional, consisting of subscales measuring cancer specific aspects of physical well-being, emotional well-being, social well-being, functional well-being, and 10-items measuring breast cancer specific concerns.

##### Fatigue

Fatigue is measured using the validated 13-item FACIT (Functional Assessment of Chronic Illness Therapy) Fatigue scale, which assesses self-reported tiredness, weakness and difficulty conducting usual activities
[54].

#### Social cognitive mediators of physical activity

Hypothesized social cognitive mediators of PA behaviour are assessed using previously published, validated instruments where possible. Some items were adapted to make them more appropriate for use in this study. The adaptations were based on our own qualitative research and formative research in the field (e.g.
[55]) and were tested for face validity using a small convenience sample (n = 5) of post-treatment breast cancer survivors. In each survey, the time referent used for the items is framed based on the timing of the proceeding follow-up survey (i.e. the baseline survey time referent is “the past/next four months” and the four and ten month follow-up surveys time referent is “the past/next six months”).

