### Randomisation

The randomisation sequence will be generated by a statistician (PM) using SAS 9.2 statistical software. An equal number of participants will be randomised to each group (1:1:1) using a randomised block design, with a block size of six, to ensure the study groups are balanced
[39,40].

Participants, identified only by their ID number, will be randomised by an administrative staff member into groups upon receipt of their baseline survey. All project team members will be blinded to this process and participant details will remain de-identified until participant allocation is completed. Participant blinding is not possible due to the difference in delivery schedule of the two interventions.

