### Outcomes

A pen-and-paper questionnaire is completed at baseline, 4 months post baseline (immediate post- tailored intervention follow-up), and 10 months post-baseline (7 month post tailored-intervention follow-up). At each of these time-points, participants will be asked to wear a pedometer for seven days and complete a step count diary.

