##### Environment

*Social support* is assessed using the 15-item social support for exercise habits scale
[61]*.* Participants are asked to rate how often during the past four months their friends and family (separately) supported them/discouraged them to exercise in a variety of ways. Response options range from 1 (none) to 5 (very often). An example item is: “During the past four months, my friends gave me encouragement to stick with my exercise program”. *The perceived built environment* will be assessed using an adapted version of the 7-item IPAQ environmental module
[62]. Participants will be asked to rate how much they agree or disagree (1 = strongly disagree to 5 = strongly agree) with the following statements: most of the houses in my neighbourhood are detached houses; many shops, stores, markets or other places to buy things I need are within easy walking distance of my home; my home is within a 10-15 minute walk to a bus or train station; there are footpaths on most of the streets in my neighbourhood; there are facilities to bicycle in or near my neighbourhood; my neighbourhood has several free or low cost recreation facilities; and the crime rate in my neighbourhood makes it unsafe to go on walks at night.

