##### Self control and performance

*Self-regulation* will be assessed using a 12-item scale developed for use among older adults
[63]. The items measure six subscales of self-regulation (self-monitoring, goal setting, eliciting social support, reinforcements, time management, relapse prevention) and can be combined to produce an overall score
[63]. An example item is “Over the past 4 months, how often did you rearrange your schedule to ensure you had time for physical activity”. Response options range from 1 (never) to 5 (very often).

*Action planning* will be assessed using 4-items developed by Rise et al.
[64] and adapted by Rhodes et al.
[65](to say “physical activity” instead of “exercise”). Participants will be asked to rate the following statements according to their plans over the next two weeks (1 = no plans to 5 detailed plans): I have made plans concerning ‘when’ I am going to engage in regular PA; I have made plans concerning ‘where’ I am going to engage in regular PA; I have made plans concerning ‘what’ kind of regular PA I will engage in; I have made plans concerning ‘how’ I am going to get to a place to engage in regular PA.

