#### Procedure

Potential participants were asked to contact the project co-ordinator to express their interest in participating in the study. Potential participants were then provided with an information statement and a consent form and asked to return it to the project team within two weeks. Information was resent at two weeks if no response was received.

Participants will be asked to complete a pen-and-paper questionnaire, wear a pedometer for seven days and complete a pen-and-paper step count diary at baseline, four and ten months from baseline (Figure
1). Participants will be instructed to return the pedometer with the written materials using a reply paid envelope as soon as possible after each assessment period is complete. Participants who do not return the baseline questionnaire, and step count diary and pedometer within two weeks will receive one reminder call from the project co-ordinator. Participants who do not return the assessment materials within three weeks after this reminder call will be excluded from the trial.

Upon receipt of the baseline questionnaire, an administrative assistant will allocate participants using the ID number written on the questionnaire into one of three groups using the randomly generated allocation sequence provided by the statistician. Participants will be sent intervention or standard recommendation materials within three weeks of allocation.

Participants in the tailored-print intervention group will be sent additional intervention materials at 6 weeks and 12 weeks post baseline and update cards (3-item update card), 4 weeks and 8 weeks post base-line and asked to return them to the research team using a reply paid envelope within 7 days. Participants in the standard recommendation group will receive one tailored newsletter and a pdf version of the targeted guidebook after completion of the10 month follow-up survey (Figure
1).

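### At 4 months the six-month look-back for social support and self-regulation reaches about two months before baseline and dilutes the raw group difference on these two mediators

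*Protocol article*

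**What the plan says.** The section on social cognitive mediators gives one rule for all surveys: "the time referent used for the items is framed based on the timing of the proceeding follow-up survey". It then states the result. At baseline, "the baseline survey time referent is “the past/next four months"; afterwards, the "four and ten month follow-up surveys time referent is “the past/next six months". The Outcomes section places the follow-up surveys at "4 months post baseline (immediate post- tailored intervention follow-up), and 10 months post-baseline".

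Two of the mediator scales ask about the past. For social support (Environment): "Participants are asked to rate how often during the past four months their friends and family (separately) supported them/discouraged them to exercise". For self-regulation (Self control and performance), the example item is "Over the past 4 months, how often did you rearrange your schedule to ensure you had time for physical activity". Both printed wordings match the baseline form.

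Under Randomisation, participants "will be randomised by an administrative staff member into groups upon receipt of their baseline survey", so any time before baseline is also before randomisation. Under Procedure: "Participants will be sent intervention or standard recommendation materials within three weeks of allocation".

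The Statistical analysis section plans ANCOVA on the socio-cognitive measures and a mediation analysis to explore how any intervention effect arises.

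**The concern.** A referent tied to the next survey suits questions about expectations and confidence. It does not suit questions about what has already happened. At month 4 the gap to the next survey (six months) is longer than the time since baseline (four months), so the backward-looking items ask partly about a period when no arm had received anything. That period also lies inside the baseline survey's own look-back.

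The tailored arm acts on both scales. Newsletter 2 advises on eliciting social support, every newsletter has an action planning activity, and the update cards assess goal setting. Goal setting and eliciting social support are themselves self-regulation subscales. If the 4-month score mixes pre-randomisation months with exposed months, the group difference on the mediator shrinks on its raw scale. The treatment-to-mediator path shrinks with it, and a real mechanism is harder to see.

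**Working it through.** **Inputs.** Surveys at months 0, 4 and 10 (Outcomes). Referents of 4, 6 and 6 months (Social cognitive mediators). Materials sent up to three weeks after allocation (Procedure).

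**1. Reproduce the plan's referents.** The gap to the next survey is 4 - 0 = 4 months at baseline and 10 - 4 = 6 months at month 4. Both agree with the stated values. Month 10 has no later survey; six months there equals the gap back to month 4.

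**2. Look-back windows.** Start of window = survey month - referent.

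| Survey | Referent | Window (months) | Share before baseline |
|---|---|---|---|
| Baseline | 4 | -4 to 0 | all, as intended |
| Month 4, as written | 6 | 4 - 6 = -2 to +4 | 2/6 = 33% |
| Month 4, past four months | 4 | 0 to +4 | 0% |
| Month 10, as written | 6 | +4 to +10 | 0% |

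The two months from -2 to 0 also fall inside the baseline window of -4 to 0.

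**3. Share after materials are sent.** Three weeks is 3/4.345 = 0.69 months. The exposed part of the 4-month window is therefore 4 - 0.69 = 3.31 to 4 months. That is 3.31/6 = 55% to 4/6 = 67% of a six-month window, against 3.31/4 = 83% to 4/4 = 100% of a four-month window.

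**4. Dilution.** Assume that respondents weight all months equally and that any change is immediate. Counting from baseline, the raw group difference is then 4/6, or two thirds, of the true one; with the three-week delay it is 55%.

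**5. Why no power figure follows.** Even averaging makes the score Y = (2/3)P + (1/3)Q, where P is the post-baseline part and Q the pre-baseline part. The effect falls to (2/3)d, but the residual variance given the baseline score falls too. If P and Q are independent given baseline:

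V = (4/9)(1 - r²) + (1/9)(1 - ρ²)

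Here r is the correlation of P with the baseline score and ρ that of Q with it. Power = Φ((2/3)d / √(2V/80) - 1.97), two-sided 0.05. The 80 per arm is 100 less 20% loss. r = 0.4 is the article's value for physical activity, borrowed here. The values of d and ρ are assumed.

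Without dilution, V = 0.84 and power is 54% at d = 0.30 and 93% at d = 0.50. With dilution:

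| Assumption on Q | V | d = 0.30 | d = 0.50 |
|---|---|---|---|
| ρ = 1 | 0.373 | 54% | 93% |
| ρ = 0.8 | 0.413 | 50% | 90% |
| ρ = 0.6 | 0.444 | 47% | 88% |
| ρ = 0.6, and P and Q correlated 0.4 overall | 0.516 | 42% | 83% |

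The last row adds 2(2/3)(1/3)(0.4 - 0.4 × 0.6) = 0.071 to V. The loss runs from none to 12 percentage points, depending on correlations that the article does not give.

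**The case against.** **The wording may be shorthand.** One phrase covers two surveys, in a condensed article, and the questionnaires are not shown. It could mean the next six months at month 4 and the past six months at month 10. The text does not say so. It names the four-month survey, and the matching phrase at baseline has to cover both directions, since the baseline items include past-four-month and next-four-month wordings. Nor do the four-month wordings printed for the two scales settle it, because they fit the baseline form. If the rule was meant to refer to the preceding survey, month 4 should read four months, and the stated six is still wrong. What stands is that the actual 4-month form cannot be seen.

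**A large loss of power.** A reader might multiply the effect by two thirds, leave the residual variance at 0.84, and infer that power for a 0.30 SD effect falls from 54% to 28%. The documents do not support this. Averaging in pre-baseline months shrinks the post-baseline noise as well, and a baseline-adjusted ANCOVA removes much of the pre-baseline part. Response error that does not average out would add some loss, but the article gives no size for it. Respondents may also favour recent months, which would lessen the dilution.

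**Bias between arms, or unequal windows.** A reader might also infer a spurious group difference. There is none to expect, because all arms answer over the same window. Nor does the different length of the baseline and 4-month windows matter much in itself: how-often ratings need not grow with window length, and ANCOVA does not require equal windows.

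**Scope.** The objection that this is narrow is right. Outcome expectations, self-efficacy and action planning look forward, and behavioural capability is asked in the present. The primary physical activity measure includes resistance items asked over the past month, and step counts cover seven days. The mediation analysis is exploratory.

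**Conclusion.** The point holds for two scales at one survey. As the rule is written, about a third of the 4-month look-back for social support and self-regulation precedes baseline and randomisation and repeats part of the baseline window. The expected consequence is a smaller raw group difference and a weaker treatment-to-mediator path on these two scales. The factor of two thirds rests on even averaging and immediate change, neither of which the article establishes. Loss of power may be small and should not be quoted as a finding. The primary comparison and the 10-month look-back stand as planned. It is a minor flaw, but worth correcting, because it affects two mechanisms that the tailored newsletters address.

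**What to change.** State the past and next referents separately in the section on social cognitive mediators. In the 4-month questionnaire, word social support and self-regulation over the past four months, and the forward-looking scales that use the survey referent over the next six months. Keep the past six months for the two backward-looking scales at month 10. Action planning has its own two-week horizon and needs no change.

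What to do depends on where the trial stands. Recruitment is complete, so this should be checked first.

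- If no 4-month forms have gone out, the cost is rewording one version of a mailed questionnaire.
- If forms with the six-month look-back are already out, keep that one version, since two versions would split a modest sample. State the pre-baseline overlap as a limitation of the 4-month mediator and mediation results. The cost is a sentence or two in the report.
- If the 4-month form already asks about the past four months, only the description in the article needs correcting.

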##### Outcome expectations

Outcome expectations is measured using 5 general items from the validated exercise pros subscale
[56] with 6-additional items developed for this study based on formative research among breast cancer survivors
[55,57], including our own qualitative research and information provided by experts in the field. The items in the scale assess the extent that individuals agree or disagree (1 = strongly disagree to 5 = strongly agree) that participating in regular PA over the next 4 month would for them: reduce tension or manage stress; increase confidence about one’s health; help to sleep better; have a more positive outlook; help control weight; regain lost strength; prevent a cancer recurrence; be enjoyable; increase fatigue; increase joint pain or result in lymphoedema. An example item includes “Over the next four months, participating in regular PA will help me prevent a cancer recurrence.”

##### Outcome expectancies

Outcome expectancies will be assessed by asking participants to rate how important each of the outcome expectations are to them (e.g. “For me, reducing joint pain is”) on a 3-point scale (1 = unimportant; 2 important; 3 very important). This scale has been utilised and tested in prior research
[44,58].

##### Self efficacy

Task self-efficacy will be assessed using 4-items developed
[57] and evaluated
[59] in previous studies with breast cancer survivors and 3 additional items developed for this study to assess task-self efficacy for resistance training activities. The items assess the participant’s level of confidence (1 = not at all confident to 5 = extremely confident) that over the next 4 months they can: walk for 20 minutes without stopping; jog for 10 minutes without stopping; climb 3 flights of stairs; exercise for 20 minutes at a level hard enough to cause an increase in heart rate; do 6 wall push ups in a row; do one small session of resistance training including 6 different exercises; and do yoga for 60 minutes (Example item: “Over the next four months, I can do 6 wall push ups in a row”).

Barrier self-efficacy will be assessed using 12-items based on previous scales used in chronic disease populations (7 items developed and tested by Rogers’ et al.
[59] among breast cancer survivors and 5 items developed and tested by Plotnikoff et al. among diabetes patients
[56,60]) and one item (“when I can’t notice any improvements in my body”) developed for this study based on formative research. Participants will be asked to rate their confidence (1 = not at all confident to 5 = extremely confident) that they can participate in regular PA over the next four months when: they lack the discipline to exercise; exercise is not a priority; the weather is bad; feeling tired; lack time; do not enjoy exercising; do not have someone to encourage them to exercise; in a bad mood or feeling depressed; have to do it alone; can’t notice any improvements in fitness; can’t notice any improvements in body; feel stiff and sore; and feel ill.

##### Behavioural capability

Behavioural capability is measured using 6-items assessing specific components of PA knowledge and skill that were developed for this study. Participants will be asked to rate on a 5-point likert scale (1 = strongly disagree to 5 = strongly agree) how much they agree with each of the statements: I know how to warm up and cool down before/after an exercise session; I have a good idea of what type of PA to do to gain health benefits; I have a good idea of how hard I should engage in PA to gain health benefits; I have a good idea of how much PA I should do to gain health benefits; I have the skills I need to engage in aerobic physical activities; and I have the skills I need to engage in resistance-based physical activities.

##### Environment

*Social support* is assessed using the 15-item social support for exercise habits scale
[61]*.* Participants are asked to rate how often during the past four months their friends and family (separately) supported them/discouraged them to exercise in a variety of ways. Response options range from 1 (none) to 5 (very often). An example item is: “During the past four months, my friends gave me encouragement to stick with my exercise program”. *The perceived built environment* will be assessed using an adapted version of the 7-item IPAQ environmental module
[62]. Participants will be asked to rate how much they agree or disagree (1 = strongly disagree to 5 = strongly agree) with the following statements: most of the houses in my neighbourhood are detached houses; many shops, stores, markets or other places to buy things I need are within easy walking distance of my home; my home is within a 10-15 minute walk to a bus or train station; there are footpaths on most of the streets in my neighbourhood; there are facilities to bicycle in or near my neighbourhood; my neighbourhood has several free or low cost recreation facilities; and the crime rate in my neighbourhood makes it unsafe to go on walks at night.

##### Self control and performance

*Self-regulation* will be assessed using a 12-item scale developed for use among older adults
[63]. The items measure six subscales of self-regulation (self-monitoring, goal setting, eliciting social support, reinforcements, time management, relapse prevention) and can be combined to produce an overall score
[63]. An example item is “Over the past 4 months, how often did you rearrange your schedule to ensure you had time for physical activity”. Response options range from 1 (never) to 5 (very often).

*Action planning* will be assessed using 4-items developed by Rise et al.
[64] and adapted by Rhodes et al.
[65](to say “physical activity” instead of “exercise”). Participants will be asked to rate the following statements according to their plans over the next two weeks (1 = no plans to 5 detailed plans): I have made plans concerning ‘when’ I am going to engage in regular PA; I have made plans concerning ‘where’ I am going to engage in regular PA; I have made plans concerning ‘what’ kind of regular PA I will engage in; I have made plans concerning ‘how’ I am going to get to a place to engage in regular PA.

#### Socio-demographics

The following socio-demographic data will be collected: date of birth, marital status, parental status, living arrangement, country of birth, education, employment, income, internet access, health insurance status and geographical location.

#### Health status and cancer history

At baseline and each follow-up time point (where applicable), participants are asked five questions about their health status (physical limitations, perceived weight, menopause status, co-morbidities) and nine questions about their cancer diagnosis (age at diagnosis, cancer stage, treatment type, and prognosis).

#### Process evaluation

Participant evaluation of the intervention materials will be measured using 15 multiple choice items and one open-ended question, included in the immediate post intervention follow-up questionnaire. The 15 multiple choice items were purpose-designed by the research team and are based on the Elaboration Likelihood Model (ELM)
[34], which is often utilised to explain the effects of health communication interventions. An example item includes: “how personally relevant was the health information you received” (1 = not at all relevant to 5 = very relevant). The open ended question provides participants with a chance to make comments about the intervention materials.

